## Abstract

**Background:**

The standard way to stop smoking is to stop abruptly on a quit day with no prior reduction in consumption of cigarettes. Many smokers feel that reduction is natural and if reduction programmes were offered, many more might take up treatment. Few trials of reduction versus abrupt cessation have been completed. Most are small, do not use pharmacotherapy, and do not meet the standards necessary to obtain a marketing authorisation for a pharmacotherapy.

**Design/Methods:**

We will conduct a non-inferiority randomised trial of rapid reduction versus standard abrupt cessation among smokers who want to stop smoking. In the reduction arm, participants will be advised to reduce smoking consumption by half in the first week and to 25% of baseline in the second, leading up to a quit day at which participants will stop smoking completely. This will be assisted by nicotine patches and an acute form of nicotine replacement therapy. In the abrupt arm participants will use nicotine patches only, whilst smoking as normal, for two weeks prior to a quit day, at which they will also stop smoking completely. Smokers in either arm will have standard withdrawal orientated behavioural support programme with a combination of nicotine patches and acute nicotine replacement therapy post-cessation.

**Outcomes/Follow-up:**

The primary outcome of interest will be prolonged abstinence from smoking, with secondary trial outcomes of point prevalence, urges to smoke and withdrawal symptoms. Follow up will take place at 4 weeks, 8 weeks and 6 months post-quit day.

**Trial Registration:**

Current Controlled Trials ISRCTN22526020

## Background

Without help, most smokers who try to stop smoking relapse within one week and only 4% of quit attempts sustain abstinence for one year[1]. The best treatment results in about 22% one year prolonged abstinence[2], and the UK National Health Service (NHS) specialist stop smoking services achieve around 15% one year abstinence[3]. NHS support in primary care achieves around 7% one year prolonged abstinence[4]. Thus, while treatment improves substantially the number who achieve abstinence, whatever method of stopping is used, return to smoking is the norm for the majority and, even with treatment, the majority of relapsers resume smoking during active treatment. Thus we have a cadre of patients who have been through treatment services many times. Currently, the NHS gives the same treatment on repeated attempts to stop as on the first attempt. Patients often choose different pharmacotherapies, but in other respects, the treatment is the same every time. A common sense view is that offering repeated courses of identical treatment that failed previously might be less effective than trying different treatment. Rapid reduction might offer a new way to quit to those who have failed previously.

The standard assumption of all smoking cessation treatment is that cessation begins on a quit day and cutting down prior to quitting is not advised. This is because of the belief that with reduction each remaining cigarette will become more rewarding and harder to give up and in the meantime the smoker will suffer a loss of motivation before reaching the point where total abstinence is attained.

Smokers, however, feel that cutting down is an appropriate way to stop smoking. In the English Smoking Toolkit Study, 57% of current smokers reported they were cutting down, of whom 26% were using nicotine replacement therapy (NRT) to assist in this[5]. 40% of quit attempts were made by cutting down first. A review of epidemiological studies suggests that cutting down does not deter people from cessation, but is associated with an increase probability of trying to quit[6]. A survey of respondents to an advertisement of people interested in cessation found that 66% planned to stop by cutting down gradually, while 13% planned to stop abruptly. In a second survey of people who responded to an advertisement for those planning to reduce smoking, 57% planned to reduce then stop[7]. A survey of American daily smokers showed that 35% tried to stop gradually while 65% tried abruptly on their last attempt[8]. Those who chose gradual cessation were as motivated to stop and as confident of success as those who used abrupt cessation. They had the same level of dependence. A recently published random sample of American smokers showed that nearly half of smokers planning to quit would choose reduction over abrupt cessation and two thirds of these were interested in using medication to assist this[9]. In these smokers, there was little interest in reduction as an end in itself, only as a means to stop. Even among reducers not planning to stop soon, cessation was the goal of half. People who want to use gradual cessation to stop smoking soon have no NHS treatment programmes to assist with their attempt. Thus reduction as a means of stopping is likely to be popular, as well as providing another option for smokers who have tried and failed to stop previously.

### Literature Review

Observational studies have reported that those using gradual cessation were less likely to succeed than those using abrupt methods[10,11]. One reason may be, that those who chose gradual cessation as a means of quitting were less motivated to stop[12]. We therefore sought to find randomised trials. Based on Medline, Google Scholar, Psych Abstract, Society for Research on Nicotine and Tobacco abstract search, and a citation search plus contact with key authors, we identified the following trials as the only trials of abrupt and rapid reduction.

Marston & Mcfall randomised 65 students to one of four behavioural treatments, of which two were gradual reduction and abrupt cessation, but did not report smoking cessation rates[13]. In Gunther's trial, 55 smokers were randomised to reduction over five weeks and 55 to abrupt cessation after five weeks of behavioural support, followed by a further seven weeks of support[14]. The trial reports only relapse rates, but it is possible to calculate the relative risk (RR), 95% confidence intervals (CI) for unconfirmed undefined point prevalence abstinence at 12 months, which is 0.86 (0.44–1.68). Cinciripini randomised 128 people into four groups, scheduled reduction, non-scheduled reduction, scheduled smoking prior to quitting but no reduction, and normal smoking[15]. Baseline smoking rate was reduced by a third each week over three weeks. All groups received identical post-cessation cognitive behavioural therapy. The confirmed prolonged abstinence rates at 12 months were 44%, 18%, 32%, and 22% respectively. The Mantel-Haenszel (M-H) RR (95% CI) for reduction versus abrupt cessation is 1.14 (0.66–1.97). Flaxman randomised 64 participants to a 4 × 2 factorial trial[16]. Of relevance, two of the arms were gradual reduction and two abrupt cessation methods (crossed with aversive smoking, no aversive smoking). Post-cessation behavioural support was provided in each arm. The M-H RR (95%CI) for reduction versus abrupt cessation is 1.00 (0.47–2.13) for undefined unconfirmed point prevalence at six months. Cummings randomised 1895 smokers to a 2 × 2 factorial trial of daily versus unstructured self-help crossed with gradual versus abrupt quitting plan[17]. For unvalidated prolonged abstinence at six months, the M-H RR (95%CI) is 1.45 (0.87–2.42) for gradual cessation, based on exclusion of the 19% lost to follow up. The rates of loss were reported as 'fairly similar' in each arm. Cinciripini has recently completed a 3-arm study with participants randomised to cutting down with scheduled smoking and nicotine patch, nicotine patch pre-cessation treatment without reduction, or usual post-cessation patch only[18]. The results are unpublished, but preliminary data show improved cessation for the reduction arm at four weeks but no evidence of difference between the arms in abstinence at six months. The reduction arm had lower craving, fewer lapses, and less negative affect (personal communication). Hughes is also conducting a trial of reduction versus abrupt cessation with no results as yet.

A second group of studies have led to a new use of NRT for gradual cessation in a programme called Cut Down Then Stop (CDTS). Critically, the CDTS trials enrolled smokers who wanted to reduce their smoking but did not intend to stop it in the next one or six months. They were randomised to either NRT or placebo. The treatment programme gives NRT over 6–9 months for reduction and for a further three months post-cessation. The CDTS NRT programme led to improvements in six month prolonged abstinence over placebo (7% versus 3%), an RR (95%CI) of 2.06 (1.34–3.15)[19]. Six months prolonged abstinence is a standard accepted for evidence of effectiveness in smoking cessation[20]. Half of those who sustain abstinence for six months remain abstinent for their whole lives[21]. These cessation rates are lower than those achieved by the NHS smoking cessation services[22]. The key point is that these were rates achieved in smokers who said that they did not intend or want to stop imminently (and who were on average highly addicted). It is possible that the different intentions of smokers enrolled in CDTS trials and those that use the abrupt quitting method offered by the NHS explains the difference in prolonged abstinence rates (7% versus 18% six months prolonged abstinence). The CDTS studies demonstrate that reduction with NRT is more effective than without, but cannot show whether reduction or abrupt cessation is more effective.

The positive effect of pre-quit NRT has also been discovered in trials utilising the abrupt method of cessation, as outlined in the recent Cochrane review, which summarised trials that gave NRT patches for two weeks prior to quit day in addition to after cessation. The RR (95% CI) was 1.79 (1.17–2.72) compared with usual post-cessation use only[23]. In all these pre-cessation trials, NRT patch was used. Two studies used nicotine gum, with less effect[24,25]. Shiffman and Ferguson conducted a meta-analysis of four studies (three in the Cochrane review and one other) that all used pre-cessation patch treatments (1 of the studies used pre-quit nicotine patch (PQNP) for 4 weeks and the remainder used PQNP for 2 weeks). PQNP significantly increased the odds of abstinence both 6 weeks after quit date (Odds ratio (OR) = 1.96), and at 6 months (OR= 2.17)[26]. Participants were twice as likely to quit if they used PQNP, when compared to participants who started nicotine patch treatment on their quit day. Additionally post hoc observations found that in 3 of the 4 studies (relevant data were not available for the fourth study) participants treated with PQNP spontaneously reduced the amount of cigarettes they smoked, and those who reduced more of their own accord were more likely to quit. This may be because these participants were more responsive to treatment or could be further evidence that reduction can increase the chances of success in smoking cessation.

There are psychological principles that suggest that reduction might be more effective than abrupt cessation. One is shaping, obtaining a target behaviour (not smoking for the rest of one's life) by making successive approximations of the target behaviour (gradual cessation produces progressively longer periods of abstinence). The second is the cognitive psychology principle that completing a step toward a goal (reducing cigarettes per day) increases self-efficacy that increases the likelihood of completing the goal (abstinence). The third is classical and operant conditioning principles that decreasing the association of environmental cues (conditioned or discriminative stimuli) and a behaviour weakens the behaviour (smoking reduction typically uncouples cues from smoking). The fourth is the psychopathology principle that lowering drug intake reduces drug dependence increasing ability to abstain completely.

There is evidence that gradual reduction should be much more rapid than used in the CDTS trials. In one CDTS trial, Haustein (currently unpublished) participants were randomised in a 2 × 2 factorial design of NRT versus placebo and rapid versus slow reduction[27]. Despite enrolling people who said they did not intend to stop smoking in the next month, rapid reduction outperformed slow reduction at the end of trial (12 months from baseline). For confirmed 7-day point prevalence reduction, the M-H RR (95%CI) is 1.01 (0.55–1.84), confirmed prolonged abstinence it is 4.57 (1.00–20.93), and for confirmed prolonged reduction it is 2.69 (1.08–6.68). A pilot study randomised 31 smokers ready to stop to reduce over two weeks or three[28]. The quit rates were slightly higher in the two week group and qualitative data indicated that rapid reduction helped demarcate the boundary between reducing and quitting.

### Trial Objectives

#### Aim

To confirm or refute equivalence of two different behavioural instructions in stopping smoking, namely reduction or abrupt cessation.

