### Why a non-inferiority trial?

Given reduction is so intuitive and appealing; it is likely to attract smokers who would have used abrupt quitting had reduction not been available. It is imperative to show that such smokers would not be worse off if they opted for a reduction programme and we propose to test this with a non-inferiority trial. Non-inferiority trials can show superiority but conventional superiority trials cannot show non-inferiority[29]. We propose an unblinded pragmatic trial large enough to show equivalence of the methods.

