### Trial Statistics

#### Power calculation

We propose a non-inferiority trial following the Consolidated Standards of Reporting Trials (CONSORT) statement for such trials[29]. With a one-sided alpha of 0.05 we have 80% power to detect inferiority of 9.5% in the quit rate at four weeks if we enrol 343 in each arm, assuming 50% 4-week abstinence. Therefore the trial sample size shall be N = 700. Analyses will be carried out on an intention-to-treat basis, according to the Russell Standard, where participants lost to follow up are assumed to be smokers [20].

Arguably, differences of 5% at 4 weeks would be worthwhile detecting[50], but a trial would need to enrol 2500 participants for this, which would make it impractical and unlikely to be funded. If the reduction produced abstinence rates not worse than 9.5% less at four weeks, this is probably sufficient for stop smoking services to implement the programme.

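### The Aim and the size claim promise equivalence, but the trial is sized only for one-sided non-inferiority within 9.5 percentage points

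*Protocol article*

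**What the plan says.** The protocol article describes the goal in two ways.

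- **Equivalence.** The Aim, under Trial Objectives, is "To confirm or refute equivalence of two different behavioural instructions in stopping smoking, namely reduction or abrupt cessation". The section Why a non-inferiority trial? closes with "We propose an unblinded pragmatic trial large enough to show equivalence of the methods".
- **Non-inferiority.** The abstract states "We will conduct a non-inferiority randomised trial of rapid reduction versus standard abrupt cessation among smokers who want to stop smoking". The Power calculation reads "With a one-sided alpha of 0.05 we have 80% power to detect inferiority of 9.5% in the quit rate at four weeks". The number needed and the assumed rate are given there as "if we enrol 343 in each arm, assuming 50% 4-week abstinence", and the total is rounded up to 700. The margin is given on the lower side only: "If the reduction produced abstinence rates not worse than 9.5% less at four weeks, this is probably sufficient" for services to take the programme up.

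The rationale also says "It is imperative to show that such smokers would not be worse off if they opted for a reduction programme", and the same sentence goes on to say that a non-inferiority trial will test this. The Power calculation adds "Arguably, differences of 5% at 4 weeks would be worthwhile detecting", puts the cost of that at 2500 participants, and rejects it as impractical.

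**The concern.** Equivalence asks whether the arms differ by less than a margin in either direction. Non-inferiority asks only whether reduction is worse by more than a margin. The Aim poses the first question and the design answers the second.

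This goes beyond vocabulary for two reasons. First, the statement that the trial is large enough to show equivalence is a claim about power that can be checked, and no calculation in the article supports it. Second, the two questions can have different answers. The Literature Review sets out four psychological principles by which reduction might work better than abrupt cessation. If it did, the planned test would succeed while the stated Aim failed.

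At stake is what a positive result may be said to show. The rationale is about smokers who would otherwise have quit abruptly, and services would decide for them on the strength of the conclusion. An Aim worded as equivalence leaves room for a stronger conclusion than the design can carry.

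**Working it through.** **Inputs, all from the Power calculation:** one-sided alpha 0.05 (z = 1.645), power 80% (z = 0.842), margin 0.095, abstinence 50% (taken as equal in both arms), 343 per arm needed, 700 enrolled (350 per arm at 1:1). Losses count as smokers, so no inflation applies.

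**Step 1. Reproduce the stated sample size.**
n per arm = (1.645 + 0.842)² × (0.25 + 0.25) / 0.095² = 342.5, rounded up to **343**. This matches. With 350 per arm the power for non-inferiority is 80.7%. The article's 2500 for a 5-point margin also reproduces: the same formula with 0.05 gives 1237 per arm, 2474 in total.

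**Step 2. Power for equivalence with the same participants.**
This needs an upper bound, and the article gives none. Assume it mirrors the lower one, at 9.5 points either way, with two one-sided 5% tests and truly equal arms:

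power = 2 × Φ(0.095/SE − 1.645) − 1, with SE = √(0.5/n).

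| n per arm | SE | Φ(0.095/SE − 1.645) = non-inferiority power | Equivalence power |
|---|---|---|---|
| 343 | 0.0382 | 0.800 | 60.1% |
| 350 | 0.0378 | 0.807 | 61.5% |

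With 350 per arm and a common abstinence rate anywhere from 30% to 60%, equivalence power runs from 61% to 73%, below 80% throughout.

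**Step 3. Size needed for 80% equivalence power under that assumption.**
n per arm = (1.645 + 1.282)² × 0.5 / 0.095² = 474.5, so 475 per arm, **950** in total.

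**Step 4. Where the two criteria disagree.**
With 350 per arm the one-sided 5% limit lies 1.645 × 0.0378 = 6.2 points from the estimate. Non-inferiority is met when reduction is observed to be no more than 9.5 − 6.2 = 3.3 points worse, however much better it may be. Equivalence within the assumed bounds also requires that it be no more than 3.3 points better. Any observed advantage above about 3.3 points therefore passes the planned test and fails the stated Aim.

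**Step 5. Context for the conclusion wording.**
Suppose the truth is 50% against 45%. With 350 per arm, SE = √((0.25 + 0.2475)/350) = 0.0377, and the chance of declaring non-inferiority is Φ((0.095 − 0.05)/0.0377 − 1.645) = 32.6% (32.2% with 343).

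**The case against.** The strongest defence is that the operative design is not in doubt. The abstract, the heading of the rationale section and the Power calculation all say non-inferiority, with sidedness, margin, rate and number that agree with each other. On that view equivalence is a loose word that changes no test and no number. This is right as far as it goes, and it keeps the point to one of wording. It does not rescue the Aim or the size claim, since neither carries the 9.5-point qualification.

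A second defence also stands in part: the 60% to 61.5% depends on an upper bound that the article never sets. It is therefore an illustration under a stated assumption and does not show that the trial misses a target of its own. The 80% in the Power calculation was given for the lower side only.

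Three stronger readings are tempting but not supported.

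- *That the article promises to show no loss at all.* The sentence about smokers not being worse off ties itself to a non-inferiority test. It is a motivation; only its unqualified reuse as a conclusion would be a problem.
- *That passing a true 5-point loss about one time in three is an error.* It follows from the 9.5-point margin, which the Power calculation openly prefers to 5 points and explains. The remark on 5 points is itself hedged.
- *That nothing in the plan could refute equivalence.* The Analysis section plans confidence intervals, which can be read on both sides, and decision rules may sit in a fuller document. What can be said is that the article states no upper bound and no criterion for refuting equivalence.

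**Conclusion.** The point holds as a contradiction between the stated goal and the design. The Aim and the closing sentence of the rationale claim equivalence; the trial is sized to exclude a loss of more than 9.5 points on one side. The sample size itself is not at fault: 343 per arm is correct for non-inferiority.

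If equivalence meant 9.5 points in either direction, 700 participants would give about 61.5% power (60.1% at the calculated 343 per arm), and 80% would take about 950. These figures assume the symmetric bound, one-sided 5% tests, truly equal arms and 50% abstinence. Without any stated upper bound the size claim has no support at all. The practical consequence is confined to what a positive result may be called.

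**What to change.** Three changes of wording:

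1. **Aim:** to test whether rapid reduction is non-inferior to abrupt cessation, within 9.5 percentage points of four-week abstinence.
2. **Why a non-inferiority trial?, closing sentence:** describe the trial as large enough to exclude a loss of more than 9.5 points (80% power, one-sided 5%), in place of the claim about equivalence.
3. **Conclusion:** state in advance that a positive result will be worded as ruling out a loss greater than 9.5 points at four weeks, and not as equivalence or as an unqualified statement that reducers are no worse off.

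This needs no extra participants and alters no analysis. The cost is a less favourable permitted claim. If equivalence is really intended, the alternative is to define both bounds and re-size, to about 950 participants under the assumptions above.

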#### Objectives

1) To measure smoking abstinence at 4 week, 8 week and 6 month follow-up in both the abrupt and reduction treatment arms.

2) To investigate possible mechanisms by which the behavioural advice to reduce prior to quit day achieves its effects.

## Method

All methods outlined below are in compliance with the Declaration of Helsinki as approved by the National Research Ethics Service (08/H0408/213)

### Why a non-inferiority trial?

Given reduction is so intuitive and appealing; it is likely to attract smokers who would have used abrupt quitting had reduction not been available. It is imperative to show that such smokers would not be worse off if they opted for a reduction programme and we propose to test this with a non-inferiority trial. Non-inferiority trials can show superiority but conventional superiority trials cannot show non-inferiority[29]. We propose an unblinded pragmatic trial large enough to show equivalence of the methods.

### Inclusion criteria

Participants must meet all of the following inclusion criteria to be eligible for enrolment into the trial:

1. males and females 18 years or older,

2. smokes at least 15 cigarettes or 12.5 grams of loose tobacco daily as roll your own cigarettes, or blows 15 parts per million or above on exhaled carbon monoxide (CO) reading.

3. willing to stop smoking completely in two weeks

4. evidence of a personally signed and dated informed consent document indicating that the subject has been informed of all pertinent aspects of the study and consents to participate and be randomised to either arm

5. be willing and able to comply with all study procedures.

